## Abstract

**Background:** The number of people with dementia is increasing, with huge challenges for society and health-care systems. There are no disease-modifying therapies available. There is, therefore, an urgent need to identify strategies to reduce the risk of developing dementia. Anthocyanins are a class of compounds found in dark berries and fruits with some effects that might reduce the risk for cognitive decline and the development of dementia in older people.

**Aim:** This phase II three-center, randomized, 24-week, placebo-controlled study, ongoing in Norway, aims to evaluate the safety, and efficacy of anthocyanins in modifying key dementia-related mechanisms and maintain cognitive functioning in older people at risk for dementia.

**Methods:** Participants (220 individuals aged 60–80 years) who meet the inclusion criteria (either mild cognitive impairment or two or more cardiometabolic disorders) are being enrolled in this study at three different centers in Norway. Participants are block randomized to identically appearing capsules containing 80 mg of naturally purified anthocyanins or placebo 1:1. Dosage is 2 + 2 capsules per day for 24 weeks. The primary outcome will be the quality of episodic memory score, a composite measure from the extensively validated online cognitive test battery CogTrack®, which is administered at baseline and monthly for the next 6 months. Secondary outcomes include other major scores from CogTrack, as well as a range of neuroimaging and other biomarkers. Anthocyanin metabolites will be measured in blood and cerebrospinal fluid. The change from baseline scores will be subject to a mixed model for repeated measures analysis of covariance. The primary comparison will be the contrast (difference in the least-square means) between active and placebo at the end of the study (week 24). The primary study population will be a modified intention-to-treat population (ClinicalTrials.gov, NCT03419039).

**Discussion:** This study aims to demonstrate whether there are beneficial effects of purified anthocyanins on cognition and relevant biological functions in people at increased risk for dementia. Forthcoming results may contribute to further improvement of intervention strategies to prevent or delay the onset of dementia, including a potential decision to take anthocyanins toward phase III trials.

## Introduction

Dementia has become a rising public health problem, and the global socioeconomic burden of dementia is projected to amplify (1, 2). Misfolding of proteins such as amyloid, tau, and α-synuclein are key elements in the development of the most common neurodegenerative dementias such as Alzheimer's disease (AD) and Lewy body dementia. According to the most prominent hypothesis, the misfolding and aggregation of amyloid peptides are the key initial elements in AD (3). However, this is followed by secondary changes, including inflammation (4) and oxidative stress (5), which also contribute to neuronal dysfunction. Available treatments are only symptomatic, affecting cholinergic, and glutaminergic neurotransmission with modest clinical effect. There are no disease-modifying treatments available, and several phase III trials with anti-amyloid agents have failed (6) with some mixed but slightly more promising results with phase-III aducanumab recently reported (7, 8). Also, GV-971, a sodium oligomannate, from seaweed, has received conditional approval by China's National Medical Product Administration as a new oral treatment for mild to moderate AD (9). Notably, vascular risk factors, including diabetes, hypertension, and hypercholesterolemia, are associated with cerebrovascular disease, which is an important cause of a cognitive decline in older people and also associated with neurodegenerative diseases including AD (10). It is, therefore important to explore alternative disease mechanisms, such as inflammation (4), oxidative stress (5), and improvement of microcirculation as potential novel treatment targets.

Furthermore, dysregulation of cerebral capillaries, atherosclerosis, and endothelial changes also contribute to the development of AD (11). The strongest genetic risk factor for AD, the APOE e4 allele, is related to lipid metabolism (12), and diabetes and insulin resistance are established risk factors for AD (13). There are several studies (and reviews) that indicate a decrease in dementia incidence (14, 15). Although this in itself does not indicate that lifestyle can reduce dementia development, it is possible dementia risk can be reduced by lifestyle changes such as diet and physical activity (16).

Anthocyanins, a subclass of the flavonoids found in dark berries and fruits, are among the dietary factors that may have potentially positive effects on the pathogenesis of AD. Findings from cell, animal, and human studies suggest that they have antioxidant effects (17, 18), improve the blood lipid profile (19), and also have anti-inflammatory effects (20). Also, anthocyanins have been shown to increase flow-mediated dilatation (21–23) and to cross the blood–brain barrier (24). Thus, these substances have several effects relevant to protection against key mechanisms leading to cognitive decline and dementia in older people.

Interestingly, placebo-controlled studies have reported improvement of memory functioning in older people with memory problems or even dementia, after consumption of grape juice (25), blueberry juice (26), and cherry juice (27) as the source of anthocyanins. More recently, a randomized controlled trial has concluded that food-based anthocyanidin consumption was associated with a reduced risk of AD (28). However, previously published studies have major methodological limitations, including small sample sizes, short duration, and lack of biomarkers (29).

It is therefore not clear if these promising preliminary findings can be translated into clinically meaningful effects, that is, reducing the rate of cognitive decline and risk of dementia. Thus, they need to be substantiated in studies with a more robust design.

We have therefore set up a randomized, 24-week, parallel-group placebo-controlled three-center study: anthocyanins in people at risk for dementia.

The aim is to explore the potential of anthocyanin capsules to affect cognition in older people at risk for dementia favorably and also a range of relevant neuroimaging and peripheral biomarkers such as structural MRI, fluorodeoxyglucose positron emission tomography, and inflammation, oxidative stress, lipids, and other factors in the blood, cerebrospinal fluid (CSF), and gut microbiome. Also, we measure the effects on microcirculation and endothelial elasticity. Our recent pilot study showed that the anthocyanin capsules were well-tolerated (30).

## Methods

### Trial Design

This is a phase II, three-center, randomized, 24-week placebo-controlled trial enrolling 220 people living in three major cities in Norway (Stavanger, Oslo, and Bergen).

### Recruitment

Participants are being recruited from referrals to geriatric, psychiatric, neurology, cardiology, or memory outpatient clinics at two university hospitals and from advertisements in newspapers, radio, and on various social media. Furthermore, participants are recruited from the observational Dementia Disease Initiation study (31) and by actively reaching out to general practitioners in the areas.

### Trial Population Inclusion and Exclusion Criteria

#### Inclusion Criteria

People included in the study are those aged 60 years and older having an increased risk for dementia, by having either mild cognitive impairment (MCI) according to Winblad criteria (32) with or without cardiometabolic disorders (CMD), or normal cognition and ≥ 2 of the below stated CMDs known to be associated with increased risk of cognitive impairment and dementia (33–35): Stable cardiovascular disease, cerebrovascular disease, and metabolic disorders such as hypercholesterolemia, hypertension, or diabetes mellitus. The detailed inclusion criteria are displayed in Table 1.

**Table 1 T1:** Principle inclusion and exclusion criteria for the trial.

**Inclusion criteria**	**Exclusion criteria**
Age ≥ 60 years and < 80 years and no, or on stable central nervous system medication for the past 3 monthsANDMCI according to Winblad criteria (32) *(i.e., meeting the general MCI following criteria: (a) the person is neither normal nor demented; (b) there is evidence of cognitive deterioration shown by either objectively measured decline over time and/or subjective report of decline by self and/or informant in conjunction with objective cognitive deficits; and (c) activities of daily living are preserved, and complex instrumental functions are either intact or minimally impaired)*ORhaving ≥ 2 of the following conditions known to be associated with increased risk of cognitive impairment and dementia: ➢Stable cardiovascular disease defined as coronary artery disease seen on angiogram ➢Cerebrovascular disease according to MRI criteria (i.e., presence of Fazekas score ≥2 points OR cerebral infarct (≥1 lesion) OR lacunar infarct (≥1 lesion) OR lobar microbleed (≥1 lesion), as judged by a qualified neuroradiologist) OR as visualized on CT scan for those having contraindications to MRI ➢Hypercholesterolemia, operationalized as a history of hypercholesterolemia and/or use of statin at baseline or serum cholesterol > 7 analyzed in screening blood test ➢Hypertension, operationalized as a previous diagnosis of arterial hypertension and/or use of antihypertensive drugs ➢Overweight (BMI > 25) ➢Diabetes mellitus type 1 ➢Diabetes mellitus type 2 (i.e., history of and/or use of oral antidiabetic drugs and/or HbA1c > 6.5%)	Any dementia (defined as CDR > 0.5) Other known relevant brain disease such as Parkinson's disease, normal pressure hydrocephalus, and other diseases which according to the study physician may cause cognitive decline Diagnosis of clinical stroke last 5 years Clinically significant depression, i.e., major depression or GDS-15 score ≥ 7 Unstable coronary heart disease Heart failure in need of treatment Systemic inflammatory diseases Other serious disease with expected survival < 5 years A somatic disease that might affect cognitive function adversely Usage of heparin, warfarin, Clopidogrel, or Ticagrelor or Non-Vitamin K antagonist Oral Anticoagulants Any use of Medox® during the 12 months prior to inclusion

*CAD, coronary artery disease; CDR, Clinician Dementia Rating scale; GDS, Geriatric Depression Scale; BMI, body mass index*.

#### Exclusion Criteria

The exclusion criteria are dementia; relevant brain disease such as Parkinson's disease; or other brain diseases (except AD or cerebrovascular disease), which according to the study physician (SP) may cause cognitive decline; clinically significant depression; a somatic disease that, according to the SP, might affect cognitive functioning adversely; usage of anticoagulants; and any use of the investigational product during the 12 months before inclusion. A full list of the exclusion criteria is also displayed in Table 1.

### Investigational Product

We use Medox® capsules, a standardized nutraceutical product that contains naturally purified anthocyanins from bilberry (*Vaccinium myrtillus*) and black currant (*Ribes nigrum*). The content of each capsule is as follows: 50% Maltodextrin Glucidex IT 19, 50% bilberry (*V. myrtillus*) and black currant (*R. nigrum*) extract powder with 80-mg anthocyanin citrates as the 3-O-rutinosides of cyanidin and delphinidin and the 3-O-b-galactopyranosides, 3-O-b-glucopyranosides, and 3-O-a-arabinopyranosides of cyanidin, peonidin, delphinidin, petunidin, and malvidin. Each capsule contains 80-mg anthocyanins, and the dosage chosen is four capsules, 320 mg/day, whereas the identically appearing placebo capsules contain 91% maltodextrin and 9% citric acid. This dosage has been reported to be associated with relevant biological alterations (19, 21, 30, 36) and to have good tolerability (30). The manufacturer of Medox®, MedPalett, is producing Medox® and identically appearing placebo capsules. The participants are instructed to take two capsules twice daily for 24 weeks, which are dispensed after randomization in the study. The anthocyanins and placebo capsules are identically packaged.

### Trial Procedures and Rationale

#### Screening Procedures

All potential participants are prescreened for eligibility by a telephone interview by study research assistants (SRAs) using a prescreening questionnaire. Information about the trial is mailed before the screening visit. Informed written consent is obtained before enrollment into the trial according to Good Clinical Practice principles. Participants are informed in the written informed consent forms that they have the right to withdraw from the study at any time without prejudice.

All eligible prescreened participants meet the SP and SRA for collection of relevant clinical data that include medical and psychiatric history, concomitant medications, both prescribed medications and over-the-counter medications, demographics, physical examination, and anthropometric measurements. Various blood panels are being collected, including blood count, metabolic panel, lipid panel, thyroid function tests, and blood tests related to vitamin B12 and folate serum level, and international normalized ratio for brief coagulation status assessment. These blood tests are being performed to exclude other medical illnesses, which may contribute to cognitive decline.

Cognition is assessed with the Mini-Mental State Exam, the Informant Questionnaire on Cognitive Decline in Elderly (37), and the Clinical Dementia Rating scale (38). The Geriatric Depression Scale (15 items) is also administered.

ECG, blood pressure, and pulse rate are recorded. Also, photoplethysmography, cardio–ankle vascular index, and flow-mediated dilation are performed in a subgroup.

Neuroimaging: Structural and functional brain MRI (alternatively CT scan if MRI is contraindicated) and fluorodeoxyglucose positron emission tomography imaging are performed in a subgroup of participants, dependent on the availability of relevant resources.

Venipuncture and lumbar puncture for collection, handling, and storage of blood and CSF are performed according to highly standardized operationalized procedures (see Supplementary Material). Fecal and urine samples for microbiome analyses are also collected.

Our main objectives for collecting neuroimaging and biological samples are to test whether relevant changes associated with dietary anthocyanin intake in participants with increased risk of progressive cognitive decline can be detected, for example, effects on the rate of loss of brain structure, cortical metabolic activity, and on oxidative and inflammation markers in the blood, CSF, and the microbiome.

Second, we will investigate whether any biomarker changes are associated with the various cognitive domains assessed with the cognitive tests.

We will also perform subgroup analyses to explore whether people with a CSF and/or MRI pattern typical of AD or cerebrovascular disease respond differently to anthocyanins compared with those without such changes. These biomarker analyses will be tentative, as the study is not powered for subgroup analyses but may be informative for planning a potential phase III trial.

#### Baseline Assessment

At the baseline visit, any unplanned changes in medications since the screening assessment are recorded, and any future changes are discouraged if safe.

Participants are asked to maintain their lifestyle and habitual diet during the intervention.

The capsules are then distributed to participants after randomization (see later).

The participants will be trained in performing the CogTrack® System, an online set of cognitive tests with proven utility, reliability, sensitivity, and validity (39), as well as reliable sensitivity to change over time (40); (see later). The battery of tests includes previously described tests, such as simple reaction time, choice reaction time, digit vigilance, immediate and delayed word recall and recognition, pattern separation, spatial working memory, and numeric working memory (41). The baseline test will be performed at home on two occasions before taking the first study dose and then monthly for 6 months. Collection and registration of the cognitive data will be performed securely online (39). Cognitive data are stored on secure Amazon EC2 cloud servers with encryption in transit (transport layer security) for data across services. Data will be uploaded to Google Drive, into a folder where only authorized persons from Wesnes Cognition can access using two-step verification. Once the download is complete and confirmed by the study team as received, the data will be removed from the shared folder. A copy of the data remains on the Amazon EC2 databases. Participants are instructed to perform the test at the same time of day on all occasions, usually in the morning, and to ensure testing procedures are standardized as much as possible (i.e., temperature, room, research associate, and coffee intake).

#### Randomization, Allocation and Blinding

Participants are randomized to anthocyanins or placebo in a 1:1 ratio based on stratified block randomization. The strata are made up of the combination of three treatment sites [Stavanger University Hospital [SUS], Akershus University Hospital [Ahus], Oslo, and Betanien Hospital, Bergen] and two recruitment groups, that is, those who are recruited due to CMD criteria only vs. those who are recruited due to cognitive criteria with or without CMD criteria. Within each of the six strata, the randomization is performed in blocks of varying sizes (four or six) to ensure local balance and non-predictability of allocation. The randomization lists with ID numbers and anonymous treatment arms (“A” and “B”) are produced by the study statistician and sent to the production site, which is instructed to do a random allocation (using a dice) to specify which of A and B should be the intervention arm. The capsules (anthocyanins and placebo) are produced according to the randomization lists, marked with ID numbers, and distributed to the participating centers. At the centers, the participants are numbered consecutively at their inclusion in the study. All study staff, participants, and the data analyst remain blinded to the actual treatment given until data have been analyzed.

#### Follow-Up Assessments

Participants are contacted by telephone after 4 weeks (for discussion of safety and procedures) and seen in the clinic at weeks 12 and 24 (final visit). Blood tests are also being collected at weeks 12 and 24 (and weeks 2 and 6 for those performing cardiovascular measurements). Lumbar puncture is performed at baseline and again at week 24, and cardiovascular measurements are performed at weeks 2, 6, 12, and 24. Feces and urine sampling are collected at weeks 12 and 24. All the clinical visits are recorded in the medical journal and the case report form. See the study clinical assessment summary in Table 2 and the study flowchart in Figure 1.

**Table 2 T2:** Schedule of enrollment, intervention, and follow-up of the trial.

	**Screening** **W6–0**	**Baseline** **W0**	**W2**	**W4**	**W6**	**W8**	**W12**	**W16**	**W20**	**W24**
− Informed consent − Eligibility	x									
− Randomization		x								
− Dispense trial capsules		x					x			
− Concomitant medications	x	x		x			x			x
− Heart rate − blood pressure	x		x		x		x			x
− Height − Weight − BMI	x						x			x
− ECG	x		x		x		x			x
− Neuroimaging − (MRI, FDG-PET)	x									x
− Cardiovascular measurements	x		x		x		x			x
− Blood sampling	x		x		x		x			x
− Lumbar puncture	x									x
− MMSE − CDR − GDS	x									x
− IQCODE	x									
− Stool sample − Urine sample	x						x			x
− CogTrack training	X									
− CogTrack (monthly)		x		x		x	x	x	x	x
− Telephone interview (compliance, side effects)				x						
− Compliance check (Collection of bottles/blisters)							x			x
− Adverse event monitoring				x			x			x
− Question about change in lifestyle				x			x			x

*BMI, body mass index; ECG, electrocardiogram; FDG-PET, fluorodeoxyglucose positron emission tomography; CAVI, cardio–ankle vascular index; FMD, flow-mediated dilation; PPG, photoplethysmography; MMSE, Mini-Mental State Examination; CDR, Clinician Dementia Rating scale; IQCODE, The Informant Questionnaire on Cognitive Decline in the Elderly; GDS, Geriatric Depression Scale*.

**Figure 1 F1:**
[figure not shown]
Flowchart of the trial. SUS, Stavanger University Hospital; Ahus, Akershus University Hospital; BH, Betanien Hospital, CMD, cardiometabolic disorders; MCI, mild cognitive impairment; FDG-PET, fluorodeoxyglucose (FDG) positron emission tomography (PET); CAVI, cardio–ankle vascular index; FMD, flow-mediated dilation; PPG, photoplethysmography; MMSE, Mini-Mental State Examination; CDR, Clinician Dementia Rating scale; IQCODE, The Informant Questionnaire on Cognitive Decline in the Elderly; GDS, Geriatric Depression Scale. *cardiovascular measurements are only performed at SUS and Ahus. *FDG-PET scan is only performed at SUS.

Upon the beginning of the study, a simplified version of Table 1 is distributed to the participants to enable them to follow the study phases.

#### Trial Medication Adherence and Monitoring

To be able to calculate medication adherence, the participants will be instructed to write the time and date of first and last capsule intake on the medicine package and to collect and return the remaining capsules. These need to be brought along at the next follow-up. The following formula will be used to calculate medication adherence (42):

$$\begin{array}{l} \frac{Number\;of\;capsules\;taken}{Number\;of\;capsules\;the\;participant\;should\;have\;been\;taken}x100=n\;\% \end{array}$$

The number of capsules the participant should have taken will be calculated based on the number of days between the first and last capsule intake. The remaining capsules in the package will be subtracted from the total number of capsules to yield the number of capsules taken. For example, if the participant should have taken 360 capsules but have taken 324 capsules, the medication adherence will be (324/360) × 100 = 90%. Medication adherence will be calculated between 0 and 12 weeks and from 12 to 24 weeks. Also, in the telephone interview, after 4 weeks, the intake of capsules per protocol and any adverse effects will be noted. Anthocyanin metabolites will also be measured in blood, CSF, and urine.

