### Statistical Considerations

#### Sample Size Calculations

The sample size calculations are based on published data on CogTrack (40). We will assume a Cohen's d effect size of 0.4, two-tailed testing at *p* < 0.05, at 80% power, which is considered to be a clinically relevant effect. A sample size of 110 patients per arm is required, allowing for ~10% dropout. Analyses will be adjusted for baseline scores for each test. *A priori* subgroup analyses are planned, including separate analyses of those with MCI vs. normal cognition, old vs. middle-aged (defined as above or below median age), participants with and without CMD, and those with normal and those with abnormal CSF AD markers, although the study is not powered for these analyses.

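### The adherence ratio stops counting at the participant's own last capsule, so it measures intake while on treatment and overstates exposure among those who discontinue

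*Protocol article*

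**What the plan says.** The rule is in the Protocol article, Trial Medication Adherence and Monitoring. Participants are told to "write the time and date of first and last capsule intake on the medicine package" and to bring back what is left. The numerator is the dispensed count less the returned count: "The remaining capsules in the package will be subtracted from the total number of capsules to yield the number of capsules taken". The denominator, the number of capsules due, is "calculated based on the number of days between the first and last capsule intake". The section illustrates the ratio with a case ("if the participant should have taken 360 capsules but have taken 324 capsules") that gives 90%. It then fixes two reporting periods: "Medication adherence will be calculated between 0 and 12 weeks and from 12 to 24 weeks".

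The schedule is in Investigational Product: participants are to "take two capsules twice daily for 24 weeks", which is four capsules a day. The adherence section adds an intake check in the week-4 telephone interview and the measurement of anthocyanin metabolites in blood, CSF and urine. It gives no rule for a participant who stops for good.

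**The concern.** Adherence has two parts: how completely doses are taken while treatment continues, and how long treatment continues. A denominator that ends at the last capsule captures only the first. Two participants who take every capsule, one for two weeks and one for twelve, get the same score. A participant who stops before week 12 has no first or last intake date in the second period, so the formula gives nothing there. Unless someone intervenes, that participant drops out of the second-period summary instead of counting as zero.

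This matters mainly for interpretation. Under Planned Statistical Analyses, one capsule and one follow-up assessment are enough to enter the modified intention-to-treat population, and CogTrack is completed at home every month. Early stoppers can therefore stay in the primary analysis. If the week-24 contrast is null, readers will look at reported adherence to judge whether the product did not work or was not taken. A figure that leaves out discontinuation pushes them towards the first explanation.

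**Working it through.** **Inputs**

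- Four capsules a day (Investigational Product).
- Two periods of 12 weeks, 84 days each (Trial Medication Adherence and Monitoring). Scheduled capsules: 4 × 84 = 336 per period and 4 × 168 = 672 over 24 weeks.
- Planned dropout, from Sample Size Calculations: "A sample size of 110 patients per arm is required, allowing for ~10% dropout".

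**The article's own figure.** 324/360 × 100 = 90%, as stated. At four a day, 360 capsules correspond to 90 days, which is possible when the denominator follows actual intake dates.

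**Individual participants.** Let *s* be the day of the last capsule and *e* the share of due capsules taken up to then.

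- Article's rule: 4·*s*·*e* / (4·*s*) = *e*. The stop day cancels out.
- Against the weeks 0–12 schedule: 4·*s*·*e* / 336.

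| Last capsule | Intake until then | Article's rule | Share of the 336 scheduled |
|---|---|---|---|
| Day 14 | 100% | 56/56 = 100% | 56/336 = 16.7% |
| Day 28 | 100% | 112/112 = 100% | 112/336 = 33.3% |
| Day 28 | 70% | 78.4/112 = 70% | 78.4/336 = 23.3% |
| Day 42 | 100% | 168/168 = 100% | 168/336 = 50.0% |
| Day 70 | 100% | 280/280 = 100% | 280/336 = 83.3% |
| Day 84 | 100% | 336/336 = 100% | 336/336 = 100% |

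The last row shows that the two denominators agree for anyone who continues to the visit. For the first five rows, the second period gives 0/0 under the article's rule and 0/336 = 0% against the schedule.

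**Arm mean over 24 weeks.** Assume a share *d* stops capsules, evenly spread over the 168 days, so that stoppers on average cover half the schedule. The article's rule gives *e*. The schedule gives *e* × [(1 − *d*) + *d* × 0.5].

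- *d* = 10%, *e* = 100%: 100% against 0.90 + 0.05 = 95.0%.
- *d* = 10%, *e* = 90%: 90% against 0.90 × 0.95 = 85.5%.
- *d* = 5%: 100% against 97.5%, or 90% against 87.8%.
- *d* = 20%: 100% against 90.0%, or 90% against 81.0%.

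The gap runs from about 2 to 10 points.

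**By period, as the article reports it** (*d* = 10%, *e* = 100%). Half of the stoppers, 5% of the arm, stop in each period.

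- Weeks 0–12: 0.95 + 0.05 × 0.5 = 97.5% of schedule.
- Weeks 12–24: 0.90 + 0.05 × 0.5 + 0.05 × 0 = 92.5% of schedule.
- The article's rule gives 100% in both, with 5% of the arm having no value in the second.

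The gap is therefore 2.5 points in the first period and 7.5 in the second, averaging 5.

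**The case against.** The best defence is that nothing stated in the article depends on this ratio. There is no adherence threshold, no per-protocol set and no adherence covariate. The primary population is defined without it, and the Discussion assigns the study of dose effects to metabolites in blood and CSF. The date of last intake is recorded and leftover capsules are returned, so discontinuation is not lost and any other ratio can be computed later. A detailed analysis plan is promised before unblinding.

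Most of this stands, and it limits the severity. It does not remove the point. The article does not leave the denominator open: it fixes one, and that one gives a misleading figure for discontinuers. The week-4 call and the metabolite assays are useful in themselves but do not change the reported percentage.

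Four stronger readings are tempting, and the documents do not support them:

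- A reader might infer that every early stopper scores about 100%. The score equals the intake rate before stopping; someone who took 70% scores 70%.
- A reader might infer that the trial's adherence figure is wrong throughout. It is correct for participants who continue to each visit.
- A reader might take the 360-capsule illustration as an error because 12 weeks require 336. It is a hypothetical case, arithmetically right, and fits a 90-day interval.
- A reader might object that the days between two dates are one fewer than the dosing days. Read that strictly, a full taker over 84 days scores 336/(4 × 83) = 101.2%. The effect is trivial, and the text, which says only that the count is based on the number of days, does not force that reading.

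**Conclusion.** The point holds as a defect in a descriptive measure. As defined, the ratio excludes all time after permanent discontinuation and is undefined for a period without intake, so it overstates exposure among those who stop. For one participant the gap can be large (100% against 33% for a full taker who stops on day 28). For an arm mean it is about 5 points over 24 weeks, larger in the second period than in the first. The error can only be upward.

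The arm-level figure rests on three assumptions: that the planned dropout of about 10%, which is dropout from the study, equals the share stopping capsules; that stopping is evenly spread over time; and that stoppers' packages come back so that their capsules can be counted. The article gives no discontinuation rate, hence the range of 2 to 10 points for 5% to 20% stopping.

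The primary estimate, its error rate and its power are not affected. Severity: minor to moderate.

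**What to change.** For each period, make the main adherence figure capsules taken divided by capsules scheduled. Scheduled means 4 × the days from first intake (first period) or from the start of the second period, up to the actual week-12 or week-24 visit, or to the scheduled date if the visit is missed. Score a period with no intake as 0%, so that it stays in the summary.

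Do not start the first period at dispensing. Under Baseline Assessment, capsules are handed out at the baseline visit while the home baseline tests come before the first dose, so counting from dispensing would mark participants down for days on which they were not meant to take capsules.

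Report time to discontinuation by arm alongside. Keep the present ratio as a secondary measure, labelled *adherence while on treatment*.

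The cost is one definition in the analysis plan. Intake dates, returned counts and visit dates are already collected. The only downside is that reported adherence will look slightly less favourable.
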